# Design of the DYNAMO study: a multi-center randomized controlled trial to investigate the effect of pre-thickened oral nutritional supplements in nursing home residents with dysphagia and malnutrition (risk)

**DOI:** 10.1186/s12877-020-01947-4

**Published:** 2020-12-14

**Keywords:** Geriatrics, Malnutrition, Dysphagia, Pre-thickened oral nutritional supplement, Nutritional status

## Abstract

**Background:**

Oropharyngeal Dysphagia (OD) and malnutrition are frequently reported conditions in nursing home residents, and are often interrelated. Best care for dysphagic residents with, or at risk of, malnutrition should target adequate nutritional intake and the safety and efficacy of swallowing. The effect of oral nutritional supplements (ONS) suitable for nursing home residents with concurrent OD and malnutrition (risk) on nutritional status has not been investigated before. The current study aims to investigate the effect of daily use of a range of pre-thickened ONS on the body weight of nursing home residents with OD and malnutrition (risk) compared to standard OD and nutritional care.

**Methods / design:**

The DYNAMO study is a randomized, controlled, multi-center, open label trial with two parallel groups. Study participants will be recruited in nursing homes of several care organizations in the south of the Netherlands. Study duration is 12 weeks. Residents in the control group will receive standard OD and nutritional care, and residents in the test group will receive standard OD and nutritional care with extra daily supplementation of pre-thickened ONS.

The main outcome parameter is the difference in body weight change between the control and test groups. An a priori estimation of the required sample size per group (control / test) totals 78. Other outcome parameters are differences in: nutritional intake, health-related quality of life, OD-specific quality of life, activities of daily living, vital signs, and blood nutrient and metabolite levels.

**Discussion:**

Regular ONS could address the nutritional needs of nursing home residents with malnutrition (risk), but might be too thin and unsafe for residents with OD. Pre-thickened ONS is suitable for residents with OD. It offers the advantage of being a ready-to-use amylase-resistant product available in several consistencies which are able to increase swallowing efficacy and safety. The DYNAMO study is the first to investigate the effects of pre-thickened ONS on nutritional status in nursing home residents with concurrent OD and malnutrition (risk).

**Trial registration:**

Netherlands Trial Register (NTR): NTR NL7898. Registered 24 July 2019, https://www.trialregister.nl/trial/7898

## Background

Malnutrition is frequently reported in nursing home populations, although prevalence rates vary considerably between studies, depending on the diagnostic criteria used [1, 2]. A recent study in Dutch nursing homes revealed that 20% of the residents was at risk of malnutrition [3]. A good nutritional status is essential for nursing home residents to maintain overall health, recover from disease, and optimize health-related quality of life (HRQoL) [4, 5]. Conversely, poor nutritional status, e.g. unintentional weight loss, is associated with higher morbidity [6] and mortality rates [7, 8], and lower HRQoL [9].

Nursing home residents are susceptible to malnutrition due to aging-related diseases, physiological changes in body composition and metabolism [10], care dependency [11], and swallowing impairment or eating difficulties [3]. Oropharyngeal dysphagia (OD) affects the efficacy and safety of swallowing as a result of aging-related functional bodily impairment or pathophysiological changes due to dementia, Parkinson’s disease, or stroke. A Dutch prevalence study using a standardized questionnaire revealed a prevalence rate of 12% for subjective OD symptoms [12]. Dysphagic residents are at high risk of aspiration (pneumonia), dehydration, malnutrition, and weight loss [13]. A previous study by Carrión et al. [14] described a bidirectional relationship between OD and malnutrition, with 51% of the residents having OD and malnutrition (risk). While OD affects a residents’ ability to eat, the consequences of malnutrition affect the ability to swallow; it is a vicious circle.

Nutritional care for dysphagic nursing home residents with malnutrition (risk) should thus simultaneously target adequate nutritional intake and the safety and efficacy of swallowing. Current European and Dutch guidelines for the management of OD and malnutrition suggest food fortification, oral nutritional supplementation (ONS), texture modification of solid food products, and/or thickening of liquids [15–17]. Thick, more viscous fluids tend to flow more slowly, and the assumption is that slower flow improves upper aerodigestive bolus control during swallowing. Studies suggest that increasing fluid thickness, i.e. the viscosity of the fluid, results in increased safety of swallowing, i.e. less aspiration risk [18, 19]. A more severe swallowing impairment often requires higher levels of fluid thickness to prevent aspiration [8].

The thickness of regular ONS is relatively low and is therefore not suitable for the majority of residents with OD and malnutrition (risk). The thickness of regular ONS can be further increased with a thickening powder, which is time consuming and offers an insufficient guarantee of obtaining the desired ONS thickness. Compared to regular ONS, pre-thickened ONS offers the advantage of being a ready-to-use, amylase-resistant product available in several consistencies (from drinkable to spoonable), which are able to increase swallowing efficacy and safety. A recent study showed increased product compliance and user-convenience with pre-thickened ONS compared to manually thickened ONS, with similar gastro-intestinal tolerability [20].

Benefits of ONS on nutritional status in nursing home residents with malnutrition (risk) were described previously [21–24], however no studies exist on the effect of pre-thickened ONS on swallowing in dysphagic nursing home residents. Scientific evidence on the effect of pre-thickened ONS for nutritional care in dysphagic nursing home residents having malnutrition (risk) is needed. The DYNAMO^1^ study aims to investigate the effect of daily use of a range of pre-thickened ONS for 12 weeks on the body weight of nursing home residents with OD and malnutrition (risk) compared to standard OD and nutritional care.

## Methods and design

### Study design

The current study is a randomized, controlled, multi-center, open label (no blinding) trial with two parallel groups. The study duration is 12 weeks, preceded by an enrolment period including pre-screening, informed consent, and definitive screening. A flow diagram of participants is shown in Fig. 1. If eligible, nursing home residents are randomly allocated into the control or test group directly upon screening (1:1 ratio). Nursing home residents in the control group will receive standard OD and nutritional care, and will be compared to residents in the test group receiving standard OD and nutritional care with extra daily supplementation of the test product. Measurements are performed at baseline (t_1_), 6 weeks (t_2_), and 12 weeks (t_3_). The schedule of enrolment, intervention and assessments can be found in Table 1.

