#### Blinding

Investigating the effect of the test product on top of standard OD and nutritional care precludes a (iso-caloric) control. Therefore, blinding is not possible, and all assessors need to be informed of the intervention plan of the resident. The study coordinator will be involved in the data collection process as well as in data analysis, which also precludes blinded data analysis.

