### Study outcomes

The primary outcome of the DYNAMO study is the difference in body weight change between the control and test group from baseline to final measurements after 12 weeks of intervention.

Secondary outcomes are changes in nutritional intake, HRQoL, OD-specific QoL, and patient compliance to the test product. In addition, a food diary, oxygen saturation, blood nutrient and hydration markers, blood pressure, heart-rate, upper arm and calf circumference, Barthel Index, 7-day activPAL3™, activity log, rating of the test product and dysphagia severity will be assessed.

Any (serious) adverse events ([S]AEs) will be monitored, evaluated, and documented. The relation of (S) AEs to the test product will also be evaluated by a medical doctor. Specific safety outcomes of the current study are: respiratory tract infection, urinary tract infection, dehydration, pressure ulcer, fall incident, all-cause hospitalization, and choking. An overview of study outcomes, corresponding instruments and assessment details can be found in Table 5.

**Table 5 Tab5:** Overview of study outcomes, instruments, and assessment details

	***Outcome***	***Instruments***	***Score***	***Assessment details***
***Primary***	Body Weight	Calibrated lift with integrated scale, mobile chair with integrated scale or wheelchair platform with integrated scale	Body weight weighed to the nearest gram	The resident is in fasting state and preferably dressed in light clothing and without shoes
***Secondary***	Nutritional intake	Standardized three-day food diary and a kitchen scale	Food products weighed to the nearest gram	Food products, leftovers and napkins with spit out food pieces will be weighed by a member of the trained study team
	HRQoL and OD-specific QoL	Standardized questionnaire EQ-5D-5L [33] and VAS: EQ VAS, DSS, DHRQoL [34, 35] and DAS	EQ-5D descriptive system [no problems/slight problems/moderate problems/severe problems/extreme problems] EQ VAS [0–100 score], DSS [0–10 score], DHRQoL [0–10 score], DAS [0–10 score]	Self-assessment or proxy-assessment
	Compliance to test product	Standardized compliance log	Amount of product leftover [no leftover/quarter/half/three quarters/complete leftover]	Filled out by nursing staff
***Exploratory***	ADL	Validated Barthel Index (BI) [36]	0 [dependent] - 20 [independent]	Conducted by a member of the trained study team

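### As the text orders events, residents are randomised before the t1 baseline in an open-label trial, which exposes the food-diary and quality-of-life baselines to knowledge of the arm

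*Protocol article*

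**What the plan says.** All references are to the protocol article.

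- **Study design, before the study period:** "The study duration is 12 weeks, preceded by an enrolment period including pre-screening, informed consent, and definitive screening". Baseline is not listed there.
- **Study design, allocation:** "If eligible, nursing home residents are randomly allocated into the control or test group directly upon screening (1:1 ratio".
- **Study design, measurements:** "Measurements are performed at baseline (t_1_), 6 weeks (t_2_), and 12 weeks (t_3". No sentence places t1 before or after allocation.
- **Pre-screening and screening:** screening consists of the SNAQ-RC and the four-part swallowing assessment. It includes no food diary and no quality-of-life questionnaire.
- **Blinding:** "Therefore, blinding is not possible, and all assessors need to be informed of the intervention plan of the resident". The reason given is that an add-on product cannot have an iso-caloric control.
- **Study outcomes:** the primary outcome is "the difference in body weight change between the control and test group from baseline to final measurements after 12 weeks of intervention". Changes in nutritional intake, HRQoL and OD-specific QoL are secondary. Table 5 has the study team weighing food and leftovers, and the resident or a proxy rating quality of life.
- **Data analysis:** a linear mixed model, generally by intention to treat, with correction for baseline differences.

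**The concern.** A baseline serves as a reference because treatment assignment cannot have affected it. If t1 is taken once the resident, proxy, ward staff and assessor know the arm, that is no longer assured for measures that depend on judgement or behaviour. A proxy who knows that the resident will, or will not, receive the product may rate quality of life differently. Staff who know the arm may offer or record food differently over the diary days. The error could go in either direction. It enters the change from baseline directly, and correcting for a baseline that is itself affected does not remove it.

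There is also a question of who is analysed. A resident or representative who is disappointed with the allocation can withdraw before t1. That person has been randomised but has no measurements, so the mixed model has nothing to use, and the loss may depend on the arm.

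The reason given for not blinding explains open follow-up. It does not explain why allocation should be known at baseline.

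**Working it through.** **1. Order of events.** Study design lists three steps before the 12-week study: pre-screening, consent and definitive screening. Allocation comes immediately on the last of these. The first measurement of the study proper is t1. The screening section contains none of the diary or quality-of-life measures, and a three-day diary hardly fits between screening and an allocation made directly upon it. The natural reading is screening, allocation, t1. No passage contradicts this, but none states it.

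**2. Which baselines are exposed on that reading.**

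| Measure | Who produces it | Exposure at t1 |
|---|---|---|
| Three-day food diary | Study team weighs food and leftovers | Yes: offering, eating and recording can vary with the known arm |
| HRQoL and OD-specific QoL | Resident or proxy | Yes: subjective ratings by people who know the arm |
| Body weight | Calibrated scale, resident fasting | Slight: light clothing and no shoes are only a preference ("The resident is in fasting state and preferably dressed in light clothing and without shoes") |
| Compliance with the product | Nursing staff | None: there is no baseline |
| SNAQ-RC and swallowing assessment done at screening | Study procedures before allocation | None |

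**3. The plan's own sample size.** Inputs from Power calculation: difference 1.4 kg (test +1.4, control 0), SD 2.4 kg, alpha 0.05 (taken as two-sided), power 0.90, dropout 20%.

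n per group = 2 × (1.960 + 1.282)² × 2.4² / 1.4² = 61.8, rounded up to 62. Then 62 / 0.80 = 77.5, rounded up to 78. The stated figure is reproduced, and this point does not change it.

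**4. What a shift in the weight baseline would do, if there were one.** The documents give no figure, so the shifts below are assumptions, passed fully into the change score. With 62 evaluable per group, SE = 2.4 × √(2/62) = 0.43 kg.

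| Assumed between-arm error at t1 | Share of 1.4 kg | Two-sided type I error if it favours test | Power if it works against test |
|---|---|---|---|
| 0 kg | 0% | 5.0% | 90% |
| 0.1 kg | 0.1/1.4 = 7% | 5.6% | 85% |
| 0.3 kg | 0.3/1.4 = 21% | 10.7% | 72% |
| 0.5 kg | 0.5/1.4 = 36% | 21.3% | 55% |

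The table shows sensitivity only. With a calibrated scale and fasting residents, the top of the range would need clothing or similar conditions to differ systematically by arm, and nothing in the text suggests that.

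**5. Withdrawal before t1.** The 20% allowance is for dropout after randomisation, about 78 × 0.20 = 15.6 residents per group. It covers loss of numbers. It does not restore comparability if those who leave before t1 differ by arm. The documents give neither the interval between allocation and t1 nor a withdrawal rate for it, so no size can be put on this.

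**The case against.** The strongest reply is that the order is inferred. Fig. 1 and Table 1 would show where t1 sits and are missing only because figures were not reproduced, so they cannot be held against the plan. The Blinding section says assessors need to know the intervention plan, not that they know it at t1. This stands as a limit on confidence: the point rests on the prose.

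Second, the Discussion acknowledges the lack of blinding and names mitigations: random allocation, procedures standardised across arms, and an objective primary measure. This largely answers the concern for body weight, which is read from a "Calibrated lift with integrated scale, mobile chair with integrated scale or wheelchair platform with integrated scale". It does not answer it for the diary or the quality-of-life ratings, and completing t1 before allocation is not among the mitigations.

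Third, a reader might infer more than the documents support:

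- **That the primary result is materially biased.** Any figure in kilograms is assumed, and the exposure of weight is small.
- **That every secondary change is affected.** Compliance has no baseline, and the Barthel Index and circumferences are exploratory.
- **That the baseline diary includes days on the product.** No passage says so. The primary outcome is defined from baseline to 12 weeks of intervention, which suggests that baseline marks the start. Product taken on diary days would in any case understate the gain in intake and could not create a false benefit.

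Fourth, the trial began in August 2019, so a change now leaves two orders of events in one trial. This is a real cost and is counted under the fix.

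**Conclusion.** The point holds in a limited form. On the natural reading of Study design, allocation precedes t1 in a trial where assessors must know the arm. This exposes the baselines of the food diary and of HRQoL and OD-specific QoL, and it allows residents to leave after allocation with no data for the intention-to-treat model. The exposure of the primary outcome is slight and comes mainly from weighing conditions that are stated only as a preference.

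No size can be derived from the documents. The conclusion assumes that the schedule in Table 1 agrees with the prose. If it places t1 before allocation, only a clarifying sentence is needed. The point is still worth acting on because open-label treatment does not require this order and the remedy mainly rearranges procedures already planned.

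**What to change.** For residents enrolled after the Covid-19 pause, complete the t1 measurements once definitive screening confirms eligibility, and only then release the ALEA allocation and start the intervention. If the full t1 set cannot come first, take at least the t1 body weight, quality-of-life questionnaires and food diary before allocation is disclosed. State the order in Study design. If the schedule already has t1 first, that sentence alone closes the point.

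**Cost.** Allocation is delayed by the days needed for t1: at least three for the diary, and longer if the 7-day activity recording is included. Some residents may withdraw before randomisation. This does not bias the comparison, but more residents may have to be screened. Residents enrolled earlier keep the old order. Their number should be reported, and a sensitivity analysis can check whether results differ by order of events.

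Using a screening weight as the primary baseline is not a free alternative. The text says only that the SNAQ-RC includes BMI, so a weighing under Table 5 conditions at screening would be an added requirement.

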**Fig. 1 Fig1:**
[figure not shown]
Flow diagram of participants of the DYNAMO study. Abbreviations: short nutritional assessment questionnaire for residential care (SNAQ-RC), oral nutritional supplementation (ONS)

**Table 1 Tab1:**
[figure not shown]
Schedule of enrolment, intervention and assessments. Abbreviations: short nutritional assessment questionnaire for residential care (SNAQ-RC), health-related quality of life (HRQoL), oropharyngeal dysphagia-specific quality of life (OD-specific QoL)

### Study population

The study will be carried out in nursing homes of several care organizations in the south of the Netherlands. Participants of the study will be nursing home residents that meet the eligibility criteria (Table 2). All eligibility criteria, except for OD and malnutrition (risk), will be verified by the nursing home physician using the electronic patient file.

**Table 2 Tab2:** Eligibility criteria for the DYNAMO study

Inclusion criteria	Exclusion criteria
• Permanent admission to or living in a somatic or psychogeriatric ward • ≥ 65 years of age • Risk of malnutrition, or malnutrition • Oropharyngeal dysphagia • Informed consent	• Daily use of protein- and energy-containing ONS over a period of four weeks prior to screening • Daily use of enteral or parenteral nutrition over a period of four weeks prior to screening • Renal disease requiring dialysis • Both lower legs amputated • Known allergy or intolerance to any ingredient of the test product • Participation in any other study within 6 weeks prior to or after randomization • Known cachexia • Uncertainty about the willingness or ability of the resident to comply with the protocol requirements

### Pre-screening and screening

Nursing home residents who meet any of the exclusion criteria (Table 2) will be excluded during pre-screening. Pre-screening will be conducted by a member of the trained study team.

The validated short nutritional assessment questionnaire for residential care (SNAQ-RC) [25] will be used as the screening tool for malnutrition (risk). The SNAQ-RC includes body mass index (BMI), unintended body weight loss, care dependency in feeding, and loss of appetite.

A swallowing assessment will be carried out by a speech and language therapist (SLT) to screen nursing home residents for clinically relevant signs of OD. The swallowing assessment consists of four parts that are illustrated and clarified in Table 3. Based on this swallowing assessment, the SLT determines the presence of OD and appropriate thickness of the test product.

**Table 3 Tab3:** Content of the swallowing assessment. Abbreviations: 3 oz water swallow test (3-oz WST), Water Swallow Test (WST), McGill Ingestive Skills Assessment (MISA)

	Assessment	Assessment details
**Part I**	3-oz WST [26]	• Resident is asked to drink a glass of 3 oz. of water at room temperature while seated • SLT assesses whether glass is emptied without interruption and without signs of impaired swallowing such as impaired oropharyngeal bolus transit, oral cavity pooling, coughing, drooling, and voice change
**Part II**	Structured observation of oral intake	• Observation during a meal including solid as well as liquid products • SLT focuses on maintenance of body posture, self-feed ability, and signs of impaired swallowing, and observations will be documented
**Part III**	WST with different thickness levels	• Water boluses with different thickness levels are prepared: water + thickening powder • Resident is asked to swallow at least three subsequent sips of the thickened bolus. • SLT determines the appropriate thickening of liquids for safe swallowing, i.e. the thickness at which the resident is able to swallow without showing signs of impaired swallowing
**Part IV**	Modified version of the MISA [27]	• Evaluation of functional ingestive skills of older persons: maintenance of symmetrical body posture and adequate head position for feeding, ability to grasp and use utensil and cup/glass functionally, appropriately-sized mouthfuls, voice quality after drinking, airway clearance after drinking, quantity of food remaining in mouth after swallowing, location of food remaining in mouth after swallowing, voice quality after earing, airway clearance after solids, ability to eat regular solids, soft solids, puree and pudding, and ability to drink water, thin juices, nectar, honey and pudding

### Randomization

Eligible nursing home residents will randomly be allocated to the control or test group using the online randomization tool ALEA™ (ALEA Clinical by FormsVision, Abcoude, the Netherlands). Block randomization will be performed with 1:1 allocation based on nursing home (site) and type of resident (legally capacitated vs. legally incapacitated to act for oneself) and varying block sizes of two and four.

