### State of the study

The study was initiated on the 22nd of August, 2019. The study will proceed with inclusion after Covid-19 and reopening of the centers.

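### Blocks of two and four within home and legal capacity, published before inclusion resumed, make the next allocation easier to guess than it needs to be in an open-label trial

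*Protocol article*

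**What the plan says.** The Randomization section states that "Block randomization will be performed with 1:1 allocation". The strata are the combinations of home and legal capacity, and the scheme uses "varying block sizes of two and four". Allocation is obtained "using the online randomization tool ALEA™". The probability of each block size is not given, nor is the number of homes.

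Study design describes a "randomized, controlled, multi-center, open label (no blinding) trial with two parallel groups", and Blinding adds that "all assessors need to be informed of the intervention plan of the resident".

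On entry, Study design places pre-screening, consent and definitive screening before allocation. Pre-screening and screening has a member of the study team carry out the pre-screening at which exclusion criteria are applied. One of those criteria, in Table 2, is a judgement: "Uncertainty about the willingness or ability of the resident to comply with the protocol requirements". Study population has the nursing home physician verify all criteria other than dysphagia and malnutrition risk from the patient file.

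The article is dated 14 December 2020. State of the study reports a start on 22 August 2019 and says: "The study will proceed with inclusion after Covid-19 and reopening of the centers".

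**The concern.** The online tool hides the list, but not what can be worked out from earlier allocations that everyone in the home can see. With blocks this short, one rule is enough: the arm that is behind in this home and capacity group is likely to come next. Publishing the sizes tells staff that the rule works.

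A person who expects a given arm could bring forward, delay or pass over a resident, or lean one way on the judgement about compliance. If that were done consistently, the arms would differ at entry in expected weight change. The Discussion answers the lack of blinding with random allocation, standardised procedures and an objective outcome. An objective weight does not correct for who was enrolled, and random allocation is the very protection that predictability weakens.

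**Working it through.** **Inputs.** Block sizes 2 and 4, 1:1, strata home × legal capacity (Randomization); open label (Study design, Blinding); 78 per group, 1.4 kg, SD 2.4, 20% dropout (Power calculation). Assumed: probability p = 1/2 that a block has size two (range 1/3 to 2/3), and 6 to 12 residents per stratum. With 2 × 78 = 156 residents, that means 156/12 = 13 to 156/6 = 26 strata, or about 7 to 13 homes.

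**The plan's own figure.** The article gives no figure for predictability. Its sample size reproduces: 2 × (1.960 + 1.282)² × 2.4² / 1.4² = 61.8, so 62 per group; 62/0.8 = 77.5, so 78. This point does not change it.

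**Second allocation in a stratum.** It is opposite to the first with probability p × 1 + (1 − p) × 2/3. For p = 1/2 this is 0.833; for p = 1/3, 0.778; for p = 2/3, 0.889.

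**Third (p = 1/2).** With probability 1/6 the first two are alike; the block must then be of four and the next two are certain. Otherwise the arms are level and the guess is a coin toss: 1/6 × 1 + 5/6 × 0.5 = 0.583.

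**Fourth (p = 1/2).** If the arms were level after two, the first block was of two with probability 0.5/(5/6) = 0.6. The fourth is then guessed with probability 5/6; otherwise it closes a block of four and is certain. So 1/6 + 5/6 × (0.6 × 5/6 + 0.4 × 1) = 0.917.

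**Whole stratum.** Exact enumeration for a guesser who knows the possible sizes and sees past allocations, with sizes equally likely:

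| | Blocks 2/4 | Blocks 4/6/8 |
|---|---|---|
| Second allocation correct | 83% | 61% |
| Fourth allocation correct | 92% | 78% |
| Odd positions correct | 50% to 58% | 50% to 61% |
| Overall correct, first 6 / 8 / 12 | 70.8 / 71.4 / 71.6% | 64.8 / 66.2 / 66.5% |
| Certain, first 6 / 8 / 12 | 8.3 / 9.4 / 9.9% | 1.0 / 2.9 / 2.4% |

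For p from 1/3 to 2/3, the first eight with blocks 2/4 give 70.7% to 72.3% correct and 11.7% to 6.8% certain. Fixed blocks of four give 70.8% and 33%.

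**Where the arms are unequal.** Over the first eight this is 55% of allocations with 2/4, guessed correctly 89% of the time. With 4/6/8 it is 62% of allocations, guessed correctly 76% of the time.

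**What could be at stake (illustration only).** Suppose that every such guess were acted on: residents with expected weight change +h enter when test is expected and −h when control is expected. The spurious difference between arms is 2 × share × (2 × accuracy − 1) × h. With 2/4 this is 2 × 0.547 × (2 × 0.89 − 1) × h = 0.85h; with 4/6/8 it is 2 × 0.619 × (2 × 0.761 − 1) × h = 0.65h. For h from 0.1 to 0.5 kg, 2/4 gives 0.09 to 0.43 kg. The upper end equals about one standard error, 2.4 × √(2/62) = 0.43 kg, and is under a third of the 1.4 kg target. The documents give no value for h; acting on every guess is the extreme case.

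**Precision cost of larger blocks.** A stratum of n residents with arm difference D loses a fraction D²/n² of its information when strata are fitted. In an assumed 16 strata of 9 or 10, simulation gives an average D² of about 0.59 with 2/4 and 1.32 with 4/6/8. The losses are about 0.59/9.75² = 0.6% and 1.32/9.75² = 1.4%, a difference of about 0.8%, or roughly one resident in 156.

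**The case against.** The strongest defence has four parts.

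- **Varied sizes are already a safeguard.** This stands in part. Certainty falls from 33% with fixed fours to about 9%, because staff cannot see which block size is running. The overall guess rate stays at about 71%, the same as fixed fours.
- **Eligibility is spread over several people and precedes allocation.** This stands as mitigation. The physician verifies the compliance criterion, a therapist determines dysphagia, and consent and a four-part swallowing assessment fall between pre-screening and allocation. A guess made at pre-screening loses value if someone else in the stratum is randomized meanwhile. But study staff still pre-screen, the physician may know past allocations, and the order and timing of approaching residents remain open. Because the sequence is already in the plan, asking for eligibility to be locked first would add little.
- **Small blocks keep the arms balanced within homes whose routine care differs.** That is a fair reason for them, but the precision at issue is under 1%.
- **Larger blocks help only modestly.** True; the fourth allocation would still be guessed in 78%.

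A reader might infer that the next allocation is generally known, or that the test arm has been loaded with residents likely to take the supplement. The documents support neither. About nine allocations in ten are not certain, odd positions are near a coin toss, and nothing in the article shows selective enrolment or its direction.

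**Conclusion.** The point holds as an avoidable weakness of moderate size. Under equal mixing and strata of 6 to 12, a guesser is right at the second allocation in 83% (78% to 89% across the mixing range), in about 71% overall, and with certainty in 8% to 10%. The mixing probabilities and stratum sizes are assumptions, but the overall rate hardly moves across the ranges tried. Harm also requires staff who track allocations within a stratum and act on them. The planned safeguards make that less likely but do not exclude it. The sample size is unaffected.

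**What to change.** For all inclusions after the reopening, drop blocks of two. Use larger, randomly varied blocks (for example 4, 6 and 8) or minimisation with a random element. Do not disclose the new parameters to the sites, and do not publish them until recruitment ends. The published sizes cannot be withdrawn, so changing them is the only way to make that knowledge useless. Include home and legal capacity as factors in the primary analysis.

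The cost is a protocol amendment, a change of scheme mid-trial that may leave blocks open in some strata, and slightly larger imbalance within strata, with about 0.8% loss of precision in the layout assumed above. In return, overall guessing falls from about 71% to 66%, the second allocation from 83% to 61%, and certain allocations from roughly 10% to 1% to 3%.
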